## Abstract

**Background:**

Radical prostatectomy is the gold standard treatment for men with localized prostate cancer. This technique is associated with post-operative urinary incontinence. Pelvic floor physiotherapy is a conservative, painless and economical treatment for this specific situation. Kegel exercises and perineal electrostimulation are common techniques to train pelvic floor muscles. The perineal electrostimulation can be applied to the patient with surface electrodes or by an intra-cavitary anal probe. This study proposes that transcutaneous perineal electrostimulation is as effective as intra-cavitary electrostimulation in reducing urinary incontinence secondary to radical prostatectomy. The main objective is to compare the efficacy of the treatment with transcutaneous perineal electrostimulation versus the same intra-cavitary treatment to reduce the magnitude of urinary incontinence after radical prostatectomy, and the impact on the quality of life.

**Methods:**

This single-blind equivalence randomized controlled trial will include 70 man who suffer urinary incontinence post radical prostatectomy. Participants will be randomized into surface electrodes group and intra-anal probe group. The groups will receive treatment for 10 consecutive weeks. Outcomes include changes in the 24-h Pad Test, and ICIQ-SF, SF-12 and I-QoL questionnaires. Clinical data will be collected at baseline, 6 and 10 weeks after the first session, and 6 months after the end of treatment.

**Discussion:**

The results will allow us to prescribe the most beneficial perineal electrostimulation technique in the treatment of urinary incontinence derived from radical prostatectomy.

**Trial registration:**

ClinicalTrials.gov Identifier: NCT03587402. 27/06/2018

## Background

Radical prostatectomy (RP) is the gold standard treatment for men with localized prostate cancer and prostatic hyperplasia. Improvements in anatomical knowledge and surgical techniques have significantly reduced post-intervention morbidity [1]. However, RP is associated with post-operative urinary incontinence (UI), that can persist for two years or longer and is associated to significant reductions in overall health-related quality of life (QoL) [2–5].

Urinary continence in men depends on the contributions from smooth muscle of the urethra and urethral constriction generated by contraction of three striated muscles: the striated urethral sphincter (SUS); puborectalis/pubovisceralis and bulbocavernosus [6]. RP inherently removes the prostatic segment of the urethra, and its smooth muscle (called the internal sphincter), and may remove or damage the SUS muscle or its innervation [7]. Continence recovery after prostatectomy is likely to require enhanced function of SUS (and other striated muscles) to compensate for the reduced smooth muscle [6, 7].

Pelvic floor muscle training (PFMT) is the most common non-invasive intervention for UI derived from a radical prostatectomy. Available published evidence demonstrates that PFMT with muscular electrostimulation (ES) has a significant positive impact on the early recovery of urinary continence after this intervention [8–10].

The perineal ES can be applied to the patient with surface electrodes or by an intra-cavitary anal probe [11]. Up to now, the most described method of application in the literature has been intra-anal [10, 12]. Each technique stimulates different anatomical points and remains unknown if both have the same effectiveness or one of them has more effect. Intra-cavitary application can be uncomfortable or annoying for patient; nevertheless, perineal surface ES could be a simple therapeutic modality, easy to apply and equal or more effective than intra-cavitary one.

The study hypothesizes that perineal surface ES is as effective as intra-cavitary ES in the reduction of UI secondary to radical prostatectomy. We aim to compare the efficacy of both techniques in reducing the magnitude of UI secondary to radical prostatectomy, and to evaluate its impact on the patients’ quality of life. Specifically we plan to estimate the amount (grams) of urine lost in 24 h to evaluate the severity of UI secondary to radical prostatectomy, and to assess the quality of life of the patients participating in the study.

## Methods

### Study design

This manuscript describes a research protocol for a single blind, equivalence randomized controlled clinical trial. Equivalence trials aim to determine whether one intervention is therapeutically similar to another; equivalence is defined as the treatment effect being between − Δ and + Δ, Δ meaning the margin of equivalence. If the confidence interval of the outcomes difference between the two studied groups falls within the predetermined margin of equivalence (− Δ to + Δ), the two types of techniques can be considered equivalent. Participants will be randomly allocated into surface electrodes group (intervention group, IG) and intra-anal probe group (control group, CG). The investigator performing the statistical analyses will be blinded.

### Study locations

This trial will take place at RAPbarcelona pelvic floor specialized physiotherapy centre in Barcelona, and at the pelvic floor rehabilitation unit of the Institut Mèdic Tecnologic of Barcelona.

### Study population

Patients who consult in one of the two participating centres for UI derived from a radical prostatectomy surgical intervention will be invited to participate during his first physiotherapy visit.

To be eligible, participants must meet the following criteria. Inclusion criteria: having undergone radical prostatectomy, presenting involuntary urine losses after radical prostatectomy intervention (UI grade I, II or III), do not exceeding the year since the surgical intervention, and accepting to participate in the study granting signed informed consent. Exclusion criteria: following a pharmacological treatment for UI, presenting anatomical malformations of the pelvic floor musculature, carrying a pacemaker, presenting anal fistulas, suffering serious psyche disorders, having a history of lower urinary tract infections, requiring radiotherapy as adjuvant treatment, being diagnosed with urethral stricture after surgery, presenting pelvic floor denervation, and suffering neuromuscular diseases.

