### Investigations

Patients who agree to participate in the study will be cited by telephone and receive ES therapy once a week. At baseline, participants will undergo an initial assessment where data on age, date of surgery, surgical intervention technique and days of catheterization will be collected. The Oxford test (to measure the pelvic floor muscular strength), the 24-h Pad Test (in order to quantify the involuntary loss of urine), the UI questionnaire ICIQ-SF, and the SF-12 questionnaire and the specific I-QoL test (to assess their quality of life) will be evaluated at first visit.

A total of ten treatment physiotherapy sessions will be held on a weekly basis (Table 1).

**Table 1 Tab1:** Treatment sessions

SESSION 1	Collection and recording of baseline data (age, intervention date and intervention technique), Oxford measurement and tests (24-h Pad Test, ICIQ-SF, SF-12, I-QoL) Delivery of the compliance form ES (10 min at 30 Hz and 5 min at 50 Hz) Explanation of the routine for home pelvic floor exercises (10 contractions maintained and 10 fast contractions to be performed three times a day)
SESSION 2	Session protocol: Registration of possible discomfort or adverse effects perceived by the patient Review of the domiciliary exercises routine and record of compliance ES (10 min at 30 Hz and 5 min at 50 Hz)
SESSION 3–5	Session protocol (as described in session 2)
SESSION 6	Collection of 24-h Pad Test data Oxford measurement Record of patient satisfaction with the treatment Session protocol (as described in session 2)
SESSION 7–9	Session protocol (as described in session 2)
SESSION 10	Session protocol (as described in session 2) Oxford measurement Collection of 24-h Pad Test data and completion of ICIQ-SF, SF-12 and I-QoL tests Record of patient satisfaction with the treatment
SESSION 11 (6 months after the end of treatment)	Collection of the 24-h Pad Test, compliance and satisfaction data

According to the allocation group, the ES technique will be applied using the Neurotrac Pelvitone® muscular electrostimulator, together with two round surface electrodes of 32 mm or an Analys Plus® anal stimulation probe of 140 mm.

In both groups, participants will be placed comfortably in a supine position with a pillow under their heads, without pants or underwear, and with the legs bent over two leg supports.

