### Random allocation of groups

A consecutive inclusion will be done until the desired sample size is reached. The generation of the random sequence will be carried out by the principal investigator using the statistical software Epidat. The randomization list will be delivered to the clinics reception desk and patients will be allocated by telephone at a 1:1 ratio (assignment by third parties).

Each participant will be assigned an identification number created for the study and linked to his treatment group. This number will allow the patient for beginning the treatment sessions. Two physiotherapists previously trained for the application of the study protocol will be in charge of the sessions.

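### Men enter at any time up to one year after surgery, but the described allocation has no strata and the crude difference comes first, which gives up precision without causing bias

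*Protocol article*

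**What the plan says.** Under Study population, the only limit on time since surgery is "do not exceeding the year since the surgical intervention". No minimum interval is given, and incontinence of any of the three grades qualifies.

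Under Random allocation of groups, "The generation of the random sequence will be carried out by the principal investigator using the statistical software Epidat". The next sentence reads: "The randomization list will be delivered to the clinics reception desk and patients will be allocated by telephone at a 1:1 ratio". One list is mentioned. No stratum, block or minimisation factor appears.

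Under Investigations, "data on age, date of surgery, surgical intervention technique and days of catheterization will be collected", so time since surgery can be derived for every man. The baseline 24-h Pad Test is recorded at the same visit.

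Under Collection, management and data analysis, the arms are compared by differences with 90% confidence intervals. Adjusted differences are an addition, with a reference to CONSORT, and the covariates are not named.

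On the course of recovery, the Background says that "RP is associated with post-operative urinary incontinence (UI), that can persist for two years or longer" and that training with stimulation "has a significant positive impact on the early recovery of urinary continence after this intervention". It gives no recovery figures by month.

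**The concern.** A man a few weeks after surgery and a man at eleven months can both enter, and they may differ in how much they will leak ten weeks later whichever route is used. With 35 men per arm and no stratification described, the arms can differ by chance in time since surgery. If the main estimate is the crude difference, variation that time since surgery could explain stays in the error term. The 90% interval set against ±22 g is then wider than it need be, in a trial planned with only 80% power. The surgery date must already be known to confirm eligibility, so using it costs almost nothing.

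**Working it through.** **Inputs from the article (Sample size):** margin 22 g; two-sided 90% interval, that is, two one-sided 5% tests; power 80%; true difference zero; 32 evaluable and 35 recruited per arm.

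**Assumed:** the Pad Test SD, which the article does not state; the correlation ρ between time since surgery and the Pad Test outcome; and the spread of entry times.

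**1. The plan's own figure.** For equivalence of two means with true difference zero, n per arm = 2 × [SD × (1.645 + 1.282) / 22]². With SD = 30 g this is 31.85, rounded up to 32. SD 29 g gives 30 and SD 31 g gives 35. The stated 32 therefore corresponds to an SD of about 29.6 to 30.1 g. Because this SD is back-solved, the calculation does not independently confirm the sample size.

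**2. Crude analysis.** SE = 30 × √(2/32) = 7.5 g. The 90% half-width is 1.645 × 7.5 = 12.3 g. Power = 2Φ(22/7.5 − 1.645) − 1 = 80.2%.

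**3. Size of a chance imbalance.** If entry is uniform over 0 to 12 months, the SD of time is 12/√12 = 3.46 months. The SE of the difference in arm means is 3.46 × √(2/35) = 0.83 months, and the 95% limit is 1.96 × 0.83 = 1.6 months. In another form: with simple randomisation and 35 per arm, the chance that the arms differ by 20 percentage points or more in the share of early entrants is about 12% if half are early, and about 9% if 30% are early.

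**4. Effect in grams.** The part of the estimate's error due to time since surgery has SD ρ × 7.5 g. Its 95% limit is 1.96 times that: 4.4 g at ρ = 0.3, 5.9 g at 0.4 and 7.4 g at 0.5. This part lies inside the 7.5 g SE and does not add to it. At ρ = 0.3, for example, 2.25² + 7.15² = 56.2, which is 7.5² apart from rounding.

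**5. Gain from removing that part.** Adjusted SE = 7.5 × √(1 − ρ²), with power as in step 2:

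| ρ (assumed) | SE (g) | 90% half-width (g) | Power |
|---|---|---|---|
| none (crude) | 7.50 | 12.3 | 80% |
| 0.2 | 7.35 | 12.1 | 82% |
| 0.3 | 7.15 | 11.8 | 85% |
| 0.4 | 6.87 | 11.3 | 88% |
| 0.5 | 6.50 | 10.7 | 92% |

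These are normal approximations and ignore the small cost of estimating one more coefficient.

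**6. What a display by stratum could show.** An even split leaves about 16 per arm per stratum. SE = 30 × √(2/16) = 10.6 g, and power = 2Φ(22/10.6 − 1.645) − 1, about 33%.

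**The case against.** The strongest reply is that nothing here is wrong. Simple 1:1 randomisation is valid, and chance imbalance is already covered by the 5% and 20% error rates. Adjusted differences are planned, and an article commonly leaves covariates, strata and block sizes to a fuller document. Most of this stands. The missing covariate names are not a fault in themselves, and the lack of strata is inferred from silence, although the section is otherwise specific about the procedure. What remains is the order that the article does state: the crude difference comes first and the adjusted one is additional.

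Three stronger readings are tempting and are not supported.

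- **Bias.** A reader might infer that imbalance could push the interval out of ±22 g when the routes are equal, or pull it in when they differ, as a threat beyond the planned error rates. Step 4 shows that this would count the same variability twice.
- **A firm shift in grams.** At 2 to 5 g per month since surgery, the 1.6-month limit gives about 3 to 8 g, or 15% to 37% of the margin. The slope is an assumption, and the limit is an extreme: one SE gives 1.7 to 4.1 g. A slope of 5 g per month would also imply ρ = 5 × 3.46 / 30 = 0.58, so time since surgery alone would explain a third of the variance. Nothing in the article shows that.
- **A stated driver of change.** The Background's remark on early recovery concerns the effect of training with stimulation. It does not say that ten-week change depends on months since surgery.

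**Conclusion.** The point holds as an improvement in precision and not as an error in the plan. As described, neither the allocation nor the leading analysis uses time since surgery, although the entry window is wide and the date is on file. The gain in power is about 5 points at ρ = 0.3 and about 12 points at ρ = 0.5; at ρ = 0.2 it is only about 2. These figures rest on the back-solved SD of 30 g, 32 evaluable men per arm, a true difference of zero and the assumed correlation. They cover time since surgery alone. Baseline Pad Test may add to the gain, but the article gives nothing from which to size that.

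A reader might also expect results by stratum to show whether equivalence holds early after surgery. With power of about 33% per stratum, they cannot.

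**What to change.** Make the primary equivalence estimate, the 90% interval set against ±22 g, the arm difference adjusted for time since surgery and baseline 24-h Pad Test. Name both covariates in advance and keep the crude difference as supportive. This can be done whether or not recruitment has started, and it costs two model terms.

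If recruitment has not begun, also stratify the list into two strata of time since surgery, using varying block sizes concealed from the principal investigator and the treating physiotherapists. Because the principal investigator is now the person who generates the sequence and also receives the referrals, someone else would have to generate it. Stratifying does not replace the adjustment: an analysis that ignores the strata would not narrow the interval.

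The downsides are small. The reception desk must read the surgery date before assigning, and blocking makes assignments slightly more predictable in a trial where the route cannot be masked from patient or therapist. Any arm difference shown by stratum should be labelled descriptive. No extra patients, visits or measurements are needed.

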### Investigations

Patients who agree to participate in the study will be cited by telephone and receive ES therapy once a week. At baseline, participants will undergo an initial assessment where data on age, date of surgery, surgical intervention technique and days of catheterization will be collected. The Oxford test (to measure the pelvic floor muscular strength), the 24-h Pad Test (in order to quantify the involuntary loss of urine), the UI questionnaire ICIQ-SF, and the SF-12 questionnaire and the specific I-QoL test (to assess their quality of life) will be evaluated at first visit.

A total of ten treatment physiotherapy sessions will be held on a weekly basis (Table 1).

**Table 1 Tab1:** Treatment sessions

SESSION 1	Collection and recording of baseline data (age, intervention date and intervention technique), Oxford measurement and tests (24-h Pad Test, ICIQ-SF, SF-12, I-QoL) Delivery of the compliance form ES (10 min at 30 Hz and 5 min at 50 Hz) Explanation of the routine for home pelvic floor exercises (10 contractions maintained and 10 fast contractions to be performed three times a day)
SESSION 2	Session protocol: Registration of possible discomfort or adverse effects perceived by the patient Review of the domiciliary exercises routine and record of compliance ES (10 min at 30 Hz and 5 min at 50 Hz)
SESSION 3–5	Session protocol (as described in session 2)
SESSION 6	Collection of 24-h Pad Test data Oxford measurement Record of patient satisfaction with the treatment Session protocol (as described in session 2)
SESSION 7–9	Session protocol (as described in session 2)
SESSION 10	Session protocol (as described in session 2) Oxford measurement Collection of 24-h Pad Test data and completion of ICIQ-SF, SF-12 and I-QoL tests Record of patient satisfaction with the treatment
SESSION 11 (6 months after the end of treatment)	Collection of the 24-h Pad Test, compliance and satisfaction data

According to the allocation group, the ES technique will be applied using the Neurotrac Pelvitone® muscular electrostimulator, together with two round surface electrodes of 32 mm or an Analys Plus® anal stimulation probe of 140 mm.

In both groups, participants will be placed comfortably in a supine position with a pillow under their heads, without pants or underwear, and with the legs bent over two leg supports.

Participants in the IG will receive the treatment through a 32-mm surface electrode attached just above the base of the penis and below the pubis, and another 32-mm surface electrode placed on the perineum (area between the end of the testicles and the anal sphincter).

Patients in the CG will receive the same treatment by means of an anal stimulation probe, which will be placed inside the rectal cavity.

#### *Description of the treatment session* (same for both groups)

15 min of perineal ES (with surface electrodes or intra-anal probe according to the allocation to IG or CG, respectively), composed of 10 min of direct current at 30 Hz frequency and a pulse width of 250 microseconds, to train the tonic fibres, and 5 min of alternating current at 50 Hz frequency and a pulse width of 250 microseconds, to train the phasic fibres.

Additionally, Kegel active exercises are going to be performed under the supervision and correction of the physiotherapist in each of the treatment sessions and also carried out at home. This regimen will consist of ten slow and maintained contractions of the perineal musculature (8–10 s) and ten fast contractions (3 s) to be done three times a day (twice in a supine position and once in a sitting or standing position) during the ten weeks the whole treatment lasts.

In each session, treatment adherence and possible adverse effects of the therapy will be identified and recorded in a database designed for the project.

The same treatment protocol will be followed in all sessions. In the sixth session the results of a second 24-h Pad test will be registered, the Oxford test delivered and the satisfaction with the treatment of each patient recorded. In the tenth session, the same tests as in the first session will be re-evaluated.

The indications for the 24-h Pad test will be given in the session previous to the scheduled for the patient to do it at home and bring the results on the following treatment session, excepting for that of session 1 that will be delivered at the time of acceptance in the study.

Six months after the end of the treatment, patients will be contacted by telephone for a final assessment with the purpose of checking whether the possible benefits of the therapy persist.

### Outcome measures

Participants will complete four study assessments: baseline, 6 and 10 weeks after first session, and 6 months after the end of treatment.

#### Primary outcome

##### Magnitude of urinary incontinence

According to the grams of urine collected in a pad with the 24-h Pad Test. This is a quantitative variable (expressed in grams) evaluated in the first, sixth, tenth and eleventh sessions of the study. The Pad test consists of weighing a clean pad in grams (by the same patient), then placing it and weighing it again after an established time (24 h). In case of needing an extra pad before the 24 h are completed, the procedure would be repeated until 24 h were reached. The increase in weight tells us about the severity of incontinence. The values for mild UI are from 1.3 to 20 g, moderate from 21 to 74 g and severe 75 g or more [13, 14].

#### Secondary outcomes

##### Severity of the urinary incontinence

Assessed with the score obtained in the questionnaire ICIQ-SF, a tool validated and translated into Spanish, specific to the study of UI, used in the basic evaluation of UI from the patient's perspective [15–22]. This is a quantitative variable evaluated in the first, tenth and eleventh sessions of the study.

##### Quality of life related to health

Measured with the SF-12 Quality of Life Scale and the I-QoL questionnaire. The SF-12 health questionnaire is a generic questionnaire. We will use the Spanish adaptation done by Alonso et al. [16, 17] of the SF-12 Health Survey [18, 19]. The SF-12 is a reduced version of the SF-36 Health Questionnaire designed for cases in which this is too long. The SF-12 is answered in an average of ≤ 2 min and the SF-36 needs between 5 and 10 min. It consists of 12 items from the 8 dimensions of the SF-36 physical function, social function, physical role, emotional role, mental health, vitality, body pain and general health status. Higher score means better quality of life. The I-QoL is a specific questionnaire, with only 22 items, that assesses different domains such as avoidance of behaviours, psychosocial impact and feeling of being ashamed. The questionnaire is assessed according to its different scales or globally, so that the higher the scores obtained, the better the quality of life shown [20, 21].

